#### Secondary outcomes

Thickness

NOC tissue integrity (skin and mucous membranes; 1101) – depth reached: The layers and structures of the skin altered by loss of tissue integrity (ulcerated area) will be evaluated by a Likert scale, with 1 being the worst possible score and 5 the best possible score.2.Pain

NOC tissue integrity (skin and mucous membranes; 1101) – Unpleasant sensory and emotional experience arising from actual or potential tissue damage or described in terms of such damage, with sudden or slow onset of mild to severe intensity, constant or recurrent, without an anticipated or predictable termination: The frequency, condition, and intensity will be evaluated by a Likert scale, with 1 being the worst possible score and 5 the best possible score.3.Overall improvement of other correlated NOC indicators

Overall improvement of the indicators for the NOC outcomes for wound healing (secondary intention; 1103) and tissue integrity (skin and mucous membranes; 1101) will also be assessed.

### Independent/exposure and confounding variables

The main exposure variable will be the tissue repair process in the CG and IG. The impact of each management strategy on the outcomes will be controlled by monitoring the following confounding variables: pharmacotherapy or co-intervention at another health facility or by another professional.

### Statistical analyses

Continuous variables will be expressed as mean and standard deviation or median and interquartile range according to the data distribution. Categorical variables will be expressed as absolute and relative frequencies. Generalized estimating equations will be used for comparisons between the weekly indicators, and the least-significance-difference post-hoc test will be used to assess the difference between weeks.

For quantitative variables with a normal distribution, the difference between the two groups will be compared by Student’s *t*-test. This test will also be used to analyze the means of the NOC results in relation to the decreased wound size and scar formation outcomes. The Pearson correlation coefficient will be used to evaluate the linear association between NOC results and primary outcomes. A nonparametric Mann–Whitney test will be used for comparison between the two groups regarding the characterization of ulcers.

To assess the effect size of the intervention, relative risks with 95% confidence intervals will be calculated. A two-tailed *P* < 0.05 will be considered statistically significant. All analyses will be performed in PASW Statistics, Version 18.0.

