### Sample size

The WINPEPI program, version 11.43, was used to calculate the sample size. A sample of 34 subjects (*n* = 17 per group) would be able to detect a 1-point difference on a NOC indicator score between group means (laser intervention versus conventional control) as significant. The indicators are scored on 5-point Likert scales (range 1 to 5), in which the lowest score represents the worst possible state and the highest score represents the most desirable state after implementation of interventions. A change in one level, i.e., one point on the Likert scale, characterizes a positive effect of the intervention implemented throughout the treatment study, according to mixed linear models and generalized estimating equations. The standard deviation common to the groups [18], with a statistical power of 80% and significance level of 5% were defined for the study. To account for possible refusals and losses to follow-up, the sample was oversized by 20%. Thus, 40 subjects (*n* = 20 per group) will be recruited.

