**Fig. 2 Fig2:**
[figure not shown]
Flow chart of study participation and interventions.ICF, informed consent form, NOC Nursing Outcomes Classification, RCT randomized controlled trial

Conventional treatment in CG participants will be provided by a staff nurse in the outpatient wound-care clinic who has clinical experience in the care of patients with venous ulcers. IG participants will be treated by a nurse who has similar clinical experience in wound care and is also a trained laser therapist. All nurses have been trained in the standard procedures for venous ulcer care and the clinical indicators of NOC outcomes to evaluate these lesions.

In both groups, an evaluation of healing will be carried out by assessing the 14 constituent clinical indicators of the NOC outcomes for wound healing (secondary intention; 1103) and tissue integrity (skin and mucous membranes; 1101). The 14 clinical indicators are foul wound odor, macerated skin, surrounding skin erythema, edema, granulation, decreased wound size, scar formation, pain, pruritus, abnormal pigmentation, thickness, necrosis, hydration/skin scaling, and exudate. Each clinical indicator will be evaluated using a 5-point Likert scale, where the lowest score denotes the worst possible outcome, and the highest score, the best possible outcome.

In both groups, patients will be monitored weekly until complete repair of the ulcer or for a maximum of 16 weeks. The frequency of LLLT application for this protocol was based on previous studies of phototherapy for chronic wounds [12–16]. The duration of treatment was determined based on the average healing period of a chronic wound [7–12].

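### The unadjusted LSD tests between weeks either do not test the laser effect or, if read as weekly comparisons between arms, leave the chance of a false-positive week uncontrolled

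*Protocol article*

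**What the plan says.** Under Statistical analyses the article states: "Generalized estimating equations will be used for comparisons between the weekly indicators". The post-hoc step follows in the same sentence: the "least-significance-difference post-hoc test will be used to assess the difference between weeks". The only significance criterion is "A two-tailed *P* < 0.05 will be considered statistically significant".

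The next paragraph of that section gives the comparison of the two groups to Student's t-test, and adds that this "test will also be used to analyze the means of the NOC results in relation to the decreased wound size and scar formation outcomes". It names no week for that test.

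The Sample size section links the longitudinal models to the treatment claim. It says that a change of one Likert level marks a positive effect of the intervention "according to mixed linear models and generalized estimating equations".

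On visits, the Study protocol section says that "patients will be monitored weekly until complete repair of the ulcer or for a maximum of 16 weeks". Both arms receive conventional treatment, and the laser is added in one. Two indicators are primary: decreased wound size and scar formation.

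**The concern.** LSD performs each pairwise test at the full 5% level. With weekly visits for up to 16 weeks there are many such tests, and nothing in the article says which of them carries the conclusion about the laser.

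The phrase on differences between weeks has two possible meanings:

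- **Time contrasts** (week against week). These describe healing over time. A significant change in the laser arm, or a change that is significant in one arm and not in the other, is not a comparison of the arms.
- **Weekly group contrasts** (laser against control at each week). These do address the laser, but with up to 16 or 17 chances per indicator to find P < 0.05.

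At stake is a report that offers an isolated significant week, or significant improvement within the laser arm, as evidence that the laser works.

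**Working it through.** **Inputs from the article.** Two-sided alpha 0.05; weekly visits up to 16 weeks; 17 per group in the sample-size calculation and 20 per group to be recruited. The plan gives no overall error rate that could be reproduced.

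**Inputs assumed.** The correlation between weeks is not given, so a range was used: first-order autoregressive (AR(1)) with 0.5, 0.8 or 0.95, and exchangeable with 0.5 or 0.8. Data are complete, with no true effect. Counting baseline as a 17th time point is also an assumption.

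**Step 1: number of week pairs for one indicator.** With k time points there are k(k − 1)/2 pairs.
- 16 weeks: 16 × 15 / 2 = 120.
- 17 time points: 17 × 16 / 2 = 136.

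**Step 2: reading as time contrasts.** In simulation, with an uncorrected robust variance, at least one false-positive week pair appears in 80% to 94% of trials. That holds only if nothing changes over time, which is implausible in treated ulcers. The figure is therefore not an error rate for the laser claim. The problem under this reading is that the test addresses a different question.

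**Step 3: reading as weekly group contrasts, independent weeks.** The chance of at least one false positive is 1 − 0.95^k.
- k = 16: 56%.
- k = 17: 58%.

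Weeks in the same patient are correlated, so these figures serve only as a reference.

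**Step 4: the same reading with correlated weeks.** The table shows the simulated share of null trials (2,000 per setting, one indicator) with at least one weekly group contrast at P < 0.05, using ordinary t-tests.

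| Correlation between weeks | 17 per arm, 17 time points | 20 per arm, 16 time points | 20 per arm, 17 time points |
|---|---|---|---|
| AR(1) 0.5 | 50.8% | 49.4% | 53.2% |
| AR(1) 0.8 | 38.4% | 38.0% | 36.2% |
| AR(1) 0.95 | 19.4% | 18.0% | 18.2% |
| Exchangeable 0.5 | 37.6% | 39.1% | 39.0% |
| Exchangeable 0.8 | 22.0% | 21.2% | 22.4% |

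The range is about 18% to 53%. It exceeds one half only when weeks are weakly correlated.

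**Step 5: how much the GEE variance could add.** The article names no variance estimator. If an uncorrected sandwich were used with a normal reference, the standard error of a single group contrast would shrink by √((n − 1)/n) for n per arm.
- 17 per arm: √(16/17) = 0.970. The error of one group contrast is 6.6%.
- 20 per arm: √(19/20) = 0.975. The error of one group contrast is 6.4%.
- Week pairs: 6.0% to 6.2% pooled over arms, 7.1% to 7.5% within one arm.

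The range in Step 4 would become 22% to 62%. Most of the inflation therefore comes from the number of tests.

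**Step 6: after correction.** One pre-specified week tested with t gives about 5%. A t reference with Bonferroni over the 16 or 17 weekly contrasts gives a 1.5% to 4.8% chance of any false-positive week.

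**The case against.** The strongest reply is that the LSD sentence most naturally means time contrasts, and that the group comparison of the primary indicators is assigned separately to Student's t-test. A false-positive week pair is then not a false claim about the laser. That is fair, and it is why the 18% to 53% is tied to the second reading only. It does not settle the matter. The Sample size section links the intervention effect to the GEE analysis, and the t-test names no week, so it leaves the same choice among weeks open.

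A second reply is that an article may leave such details to an analysis plan that is not shown. This holds for details on which the article is silent. It does not hold for LSD, which the article names. A later plan that adjusted over weeks would have to replace that choice.

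A reader might infer more than the article supports:

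- **That the standard errors are too small.** No variance estimator, working correlation or small-sample correction is stated, and mixed linear models are mentioned as well. Even an uncorrected sandwich would understate a single between-arm standard error by only about 3%.
- **That a joint group-by-week test would fail badly.** An uncorrected robust Wald test with 15 or 16 degrees of freedom does reject a true null in 46% to 67% of simulated trials. The plan mentions no such test.
- **That all 14 indicators form one confirmatory family.** Only two are primary, and the figures above are per indicator.

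The complete-data assumption is also a real limit, because monitoring stops at healing and later weeks may hold fewer patients.

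**Conclusion.** The point stands as a badly fixed method choice. LSD between weeks at P < 0.05, with no primary week and no adjustment, gives no valid basis for a laser conclusion under either reading. Read as time contrasts, its 120 or 136 pairs per indicator do not test the laser. Read as weekly group contrasts, it carries roughly an 18% to 53% chance of at least one false-positive week per indicator when the laser has no effect.

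That range rests on the assumed correlations, complete data and valid t-tests. The claim that LSD is unadjusted, and that the article states no other control over weeks, rests on the text alone. The small-sample behaviour of GEE is a secondary matter: conditional on an estimator that the article does not name, and small for a single contrast.

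**What to change.** 1. State whether the LSD step was meant for time contrasts or for contrasts between arms.
2. Base the laser conclusion on one pre-specified between-arm contrast for each primary indicator. This could be week 16, with a stated rule for scores after healing because monitoring stops then, or a single group-by-time test with few degrees of freedom. Align the Student's t-test sentence with that choice.
3. Replace LSD by Holm for the other weekly between-arm contrasts, or label them descriptive.
4. State that week-to-week tests within an arm are not evidence of a laser effect.
5. As a supporting recommendation: if an uncorrected sandwich variance would otherwise be used with 34 to 40 patients, use a small-sample correction with a t or F reference (for example Mancl-DeRouen or Kauermann-Carroll), or a linear mixed model with Satterthwaite or Kenward-Roger degrees of freedom.

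The cost is analysis wording and a little more analysis work, with no extra patients or visits. Enrolment was still open when the article was written, so the wording could be settled before the data are analysed. The price is fewer nominally significant weeks and, if item 5 applies, slightly wider intervals.

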**Methods/design:**

For this prospective randomized controlled trial, 40 adult patients of both sexes with active venous ulcers will be recruited. Subjects will be selected by the sealed-envelope method without any annotation or external identification that might refer to the type of study group. At the time of unblinding, a label with the description of the group to which the patient belongs (that is, control or intervention) will be found inside the envelope. Conventional treatment (topical medication and compressive therapy) will be offered to both groups. Additionally, the intervention group will receive adjuvant low-level laser therapy. All patients will be followed weekly until ulcer healing or for a maximum of 16 weeks. Evaluation of tissue repair will be based on 14 clinical indicators drawn from NOC for wound healing (secondary intention) and tissue integrity (skin and mucous membranes). The primary endpoint will be decreased wound size and scar formation. This laser therapy is expected to enhance the quality, speed, and effectiveness of the treatment of venous ulcers, a chronic condition. This should reduce associated costs to the health service and allow patients to resume their daily activities sooner.

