### Outcomes

#### Primary outcome

The primary outcome is decreased wound size and scar formation based on NOC outcome wound healing (secondary intention; 1103).Wound area in cm^2^ (measured as the product of the longest dimension in the cephalocaudal direction by the widest dimension), evaluated by a Likert scale, with 1 being the worst possible score and 5 the best possible score. Each Likert scale score of the Decreased wound size indicator has an operational definition that corresponds to the size in cm^2^.Wound covered with epithelial tissue (new pink or bright tissue that develops from the wound edges or as islands on the surface of the wound), evaluated by a Likert scale, with 1 being the worst possible score and 5 the best possible score.

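### The stated effect measure is a relative risk, but no listed outcome is defined as an event, and the sample size and primary test concern mean scores

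*Protocol article*

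**What the plan says.** The Statistical analyses section gives one measure of the size of the treatment effect: "To assess the effect size of the intervention, relative risks with 95% confidence intervals will be calculated". It attaches no event, score level or week to it.

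The outcomes are scores:

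- **Primary outcome:** two indicators, decreased wound size and scar formation, each scored 1 to 5. Wound area is measured in cm² but then mapped to the score: "Each Likert scale score of the Decreased wound size indicator has an operational definition that corresponds to the size in cm^2".
- **Thickness and pain (secondary):** also scored 1 to 5. For pain: "The frequency, condition, and intensity will be evaluated by a Likert scale, with 1 being the worst possible score and 5 the best possible score".
- **Third secondary outcome:** "Overall improvement of the indicators for the NOC outcomes for wound healing (secondary intention; 1103) and tissue integrity" of skin and mucous membranes, with no threshold for improvement and no stated scale of its own.
- **All 14 indicators (Study protocol section):** "Each clinical indicator will be evaluated using a 5-point Likert scale".

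The design concerns means. According to the Sample size section, 17 patients per group "would be able to detect a 1-point difference on a NOC indicator score between group means". The Statistical analyses section compares the means for the two primary indicators by Student's t-test and the weekly indicators by generalized estimating equations (GEE).

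**The concern.** The trial is sized on one quantity and tests that quantity, but names another as its effect size. A relative risk compares the proportions of patients with an event, and none of the listed outcomes is an event. Someone following the text could not produce the number without first adding a definition that the article does not contain.

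Two things are at stake. First, the 1-point difference that justified the sample is not the effect that the article says it will report. Second, cutting a 5-level score into two discards information and makes the estimate depend on the cut. The test and the reported effect could then point different ways: a significant difference in means beside a relative risk whose interval includes 1.

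**Working it through.** **1. The plan's own figure.** Inputs from the Sample size section: difference 1 point, power 80%, significance level 5%. The Statistical analyses section makes the test two-sided. The SD is taken from a citation and not stated, so it must be assumed.

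n per group = 2 × (1.960 + 0.842)² × SD² / 1² = 15.70 × SD²

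- SD 1.00: 15.7, rounded up to 16. The t-based solution is 16.7, rounded up to 17.
- SD 1.04: 15.70 × 1.082 = 16.98, rounded up to 17.

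The stated 17 per group therefore fits a comparison of two means with an SD of about 1.01 (t-based) to 1.04 (normal approximation). Because the SD is not given, this is consistency and not strict reproduction.

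**2. Is there an event anywhere?** Three candidates appear. None is tied to the relative risk.

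| Candidate | Where | How it is used |
|---|---|---|
| Complete repair | Study protocol | Ends weekly monitoring; not a listed outcome |
| One-level change in score | Sample size | Rationale for the 1-point target, tied to mixed models and GEE |
| Overall improvement | Secondary outcomes | Listed, but no threshold |

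**3. How much does the choice matter?** Assumptions: a normal latent score with SD 1, control mean 3 and treated mean 4, rounded to the 1 to 5 scale. The event is a score of k or more, so its probability is 1 − Φ(k − 0.5 − mean). The 95% interval is on the log scale with 20 per arm. Power is for two proportions at 17 per arm, by normal approximation.

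| Event | Control | Treated | Relative risk | 95% CI | Power |
|---|---|---|---|---|---|
| Score ≥ 2 | 0.933 | 0.994 | 1.06 | 0.94 to 1.20 | 0.15 |
| Score ≥ 3 | 0.691 | 0.933 | 1.35 | 0.98 to 1.85 | 0.44 |
| Score ≥ 4 | 0.309 | 0.691 | 2.24 | 1.09 to 4.60 | 0.62 |
| Score ≥ 5 | 0.067 | 0.309 | 4.62 | 0.79 to 26.97 | 0.44 |

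For the means, power at 17 per arm is Φ(1 / √(2/17) − 1.96) = Φ(2.915 − 1.96) = 0.83. That uses the latent 1-point shift.

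Rounding to five levels shrinks the shift slightly. The observed difference is the sum of the four differences in probability: 0.061 + 0.242 + 0.383 + 0.242 = 0.93 points. The score variances are 1.018 (control) and 0.843 (treated), so the pooled SD is √((1.018 + 0.843)/2) = 0.965. Power is then Φ(0.927 / (0.965 × √(2/17)) − 1.96) = 0.80. On either basis the means have more power than the best cut, at 0.62.

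**4. Sensitivity to the assumed control mean.** With a control mean of 2.5 the relative risk runs from 1.16 to 6.97 over the four cuts. With 3.5 it runs from 1.02 to 3.15. The figures move, but the dependence on the cut remains.

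**The case against.** The strongest reply is that this is a condensed article. The event, cut and week for a relative risk are commonly left to the full protocol or the analysis plan, which may fix them. That stands as far as the missing definition goes. A reader might infer that the cut will be chosen after the data are seen; the article does not say so, and an unseen plan could rule it out. The reply does not remove the mismatch. Even with a cut supplied, the article would still name a relative risk as the effect size of a trial sized and tested on means.

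It can also be said that the t-test and the GEE yield mean differences, so an interval for the 1-point target may well be reported. That is fair: the article does not exclude it, but names only the relative risk as the effect size.

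Three stronger readings are not supported:

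- **That any cut at any week is open, for either primary indicator.** Nothing in the text proposes weekly relative risks, so a count of all combinations would overstate the freedom.
- **That 20 per arm can detect only very large differences in healing.** With an exact calculation for the uncorrected chi-square test, power is 0.84 for 10% against 50%, 0.84 for 50% against 90%, and 0.82 for 60% against 95%. Healing is in any case not an event that the plan analyses.
- **That nothing in the plan bears on speed.** The abstract says: "This laser therapy is expected to enhance the quality, speed, and effectiveness of the treatment of venous ulcers, a chronic condition". This is an expected benefit and not a listed outcome, and the weekly GEE describes the course over time. What the article does not name is an analysis of time to repair.

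**Conclusion.** The point holds, and the analysis plan should be changed. The effect measure in the Statistical analyses section cannot be computed from the outcomes as defined, and it is not the quantity behind the sample size or the primary test. This conclusion rests on the text alone and needs no assumption.

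Its size can only be illustrated, because the SD and expected means are not given. Under the assumptions in the working, one treatment effect gives relative risks from 1.06 to 4.62 according to the cut. No cut has power above about 0.62 at 17 per arm, against 0.80 to 0.83 for the means. These are not forecasts for this trial.

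**What to change.** Replace the sentence on relative risks with two statements.

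1. **Primary effect.** For each primary indicator, report the between-group difference in mean score at week 16, adjusted for the baseline score, with a 95% confidence interval. The GEE already planned can supply this, with terms for group, week and baseline score. Monitoring stops at complete repair, so state that patients who heal before week 16 are carried at their healed score. A ratio of log-transformed areas would not serve, because it is undefined for a healed ulcer with area 0.
2. **Supplementary measure.** Restrict the relative risk, with the risk difference, to one prespecified event that weekly monitoring already observes: complete repair by week 16. Keep all randomised patients in the denominator, and state how patients lost before repair are counted.

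Time to complete repair by group is an optional further analysis if the sponsor wants to support a statement about speed.

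The cost is a change of wording, an interval to report and one supplementary analysis. No new visits, patients or measurements are needed, and the article describes enrolment as ongoing. The downside is that the relative risk will be imprecise with 20 per arm. In the illustration, even the best-powered cut had an interval from 1.09 to 4.60.
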